**Background**:

Approximately 8-10 million patients complaining of chest pain present to an Emergency Department (ED) annually in the United States. These patients are a challenge to healthcare providers, who are tasked with determining whether these symptoms are due to an acute coronary syndrome (ACS) or a non-ACS cause. Missing the diagnosis of ACS is associated with high rates of morbidity, mortality, and malpractice claims. Therefore, to avoid missing the diagnosis of ACS, patients with chest pain typically undergo extensive evaluations at an estimated cost of $10-13 billion annually. However, less than 10% of these patients are ultimately diagnosed with ACS. As the US healthcare system shifts towards a value-based model, it is clear that the current care patterns for acute chest pain, which fail to focus health system resources, such as hospitalization and cardiac testing, on patients most likely to benefit, are not sustainable.

In an effort to improve the quality and value of care for patients with acute chest pain, our group recently validated a risk stratification pathway, the HEART Pathway, which is designed to focus cardiac testing and admissions on higher-risk patients, who are more likely to benefit from testing. The HEART Pathway, which utilizes an easy to use clinical decision aid (the HEART score) and serial troponin measurement, has been shown to significantly reduce objective cardiac testing (stress testing and coronary angiography), shorten hospital length of stay, and increase the early discharge rate from the Emergency Department among patients with acute chest pain. These important efficiency gains occur without missing ACS and without increasing return visits to the ED or downstream admissions to the hospital over a 30 day period.

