**B. Background**

B1. Prior Literature and Studies

Coronary heart disease affects 15.8 million people in the US[^1^](#_ENREF_1) and represents a major public health dilemma**.** However, the evaluation process for this disease is inefficient. In the US, patients with symptoms of chest pain are generally evaluated in an ED. As a result, EDs care for 8-10 million patients annually with a complaint of chest pain.[^2^](#_ENREF_2)^,^ [^3^](#_ENREF_3) Of all patients presenting with chest pain, almost two thirds will be admitted to the hospital, but only 10% of these patients are ultimately diagnosed with an acute coronary syndrome (ACS).[^4-7^](#_ENREF_4) This over-triage has been estimated to cost $10-13 billion annually.[^8-10^](#_ENREF_8) Excessive admissions also contribute to hospital and ED crowding, which has been linked to an overall decrease in quality of care.[^11^](#_ENREF_11)^,^ [^12^](#_ENREF_12) This inefficiency also taxes the US in other ways such as lost productivity for affected patients and unnecessary invasive procedures. Equally important, this inefficiency consumes resources that could be diverted for other health interventions.

The evaluation of chest pain is also notoriously difficult for physicians. Despite a high rate of admissions for patients with chest pain, up to 4% of patients with acute myocardial infarction are inappropriately discharged from the ED.[^4^](#_ENREF_4) These patients, inadvertently discharged home with ACS, have higher mortality compared to those hospitalized[^4^](#_ENREF_4), emphasizing the importance of making the correct diagnosis the first time. Thus, physicians have adopted a strategy of admitting most patients with chest pain to observation units or inpatient beds for lengthy evaluations to avoid missing ACS. These practices lead to lengthy hospital stays, exacerbating hospital crowding, and increasing cost.

In response to this issue, a decision aid, called the HEART score was designed to risk stratify patients with chest pain or related symptoms without stress testing or cardiac imaging. It has five

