**Participation**

The target population is adult patients with acute chest pain or other symptoms suggestive of ACS, but without obvious ACS on ECG, who are being transported to WFBMC ED. Therefore, patients >21 years old with acute chest pain, without evidence of an ST-segment elevation myocardial infarction (STEMI) on ECG, will be included. Based on STEMI rates at WFBMC we expect less than 5% of patients with acute chest pain to be excluded due to ECG criteria.

This pilot has been selected for implementation based on collaborations across multiple disciplines including Emergency Medicine, Cardiology, and Prehospital Medicine. As a quality improvement project with broad-based support from local and state EMS systems, participation by human subjects will be part of customary care. Patients treated and transported for acute chest pain by paramedics in Forsyth, Surry, and Stokes County, specifically trained for this investigation, will have data abstracted from their EMS records. In EMS quality assurance projects, it is customary for EMS agencies to contact their patients by phone to assess their well-being. Therefore, each patient will be contacted 30-90 days following their pre-hospital encounter to determine if they have had MACE (cardiac death, acute myocardial infarction, and coronary revascularization), hospitalizations, and objective cardiac testing (stress testing and coronary angiography). Patients will also have index and outcome data abstracted from their WFBH EMR. These data will be reviewed to ensure the feasibility and accuracy of pre-hospital chest pain risk stratification by paramedics using the HEART score and i-STAT POC troponin assay. These quality assurance activities will be performed under a waiver of informed consent, obtained from the Institutional Review Board, as is currently utilized for similar quality surveillance programs at WFBH (i.e. the HEART Pathway Implementation).

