**F. Statistical Plan**

F1. Overview

The primary concept of the PARA-HEART project is to evaluate whether paramedics can be taught to calculate a HEART score accurately with acceptable intra-observer reliability (when compared to ED physician assessments). This project is a clinical pilot study in order to generate data to support a larger and non-observational implementation. If we are able to show that these scores can be reliably predict MACE and agree with ED physicians assessments, then we can start using the HEART score in the pre-hospital setting to alter care and transport triage and destination plans.

F2. Sample Size and Power

The PARA-HEART project is a clinical pilot study in which we hope to demonstrate that paramedics are able to achieve 98% sensitivity for the detection of MACE. To achieve a sensitivity of 98% with a lower bound of the 95% confidence interval that exceeds 90% we will need at least 50 patients with MACE events. Assuming a 10% MACE rate among our chest pain population,[^4-7^](#_ENREF_4) to include 50 patients with adverse events we will need a total sample size of 500 patients.

F3. Analysis Plan and Statistical Methods

The percentage of patients identified by paramedics using the HEART Score with POC troponin testing as high- and low-risk, the sensitivity, specificity, and positive and negative predictive values, positive and negative likelihood ratios, and accuracy for MACE will be calculated. Corresponding 95% exact binomial confidence intervals will be computed.

The proportion of patients receiving objective cardiac stress testing, cardiac catheterization, myocardial infarction, or cardiac death during the index hospitalization will be estimated for subjects classified as high and low risk by ED physicians and compared with those classified as high and low risk by paramedic assessment. Cardiac-related ED visits and readmission to the hospital will be calculated at 30 day follow-up. LOS will be reported using descriptive statistics, including median and inter-quartile range as this outcome tends to have a nonparametric distribution.

HEART scores calculated by the blinded primary ED provider will be compared to the HEART scores obtained by the paramedics. Raw percent agreement and kappa scores will be determined to assess intra-observer reliability. A kappa of >0.75 will be defined as excellent agreement, 0.60-0.74 will be defined as acceptable agreement, and <0.59 will be defined as unacceptable agreement.

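### F2 takes its 10% MACE rate from references that B1 cites for ACS, with no STEMI exclusion stated, so the protocol does not show that 500 eligible patients will yield 50 events

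*Protocol*

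**What the plan says.** F2 sets the precision goal as "To achieve a sensitivity of 98% with a lower bound of the 95% confidence interval that exceeds 90" percent and says that for this "we will need at least 50 patients with MACE events". It then converts events to patients: "Assuming a 10% MACE rate among our chest pain population", citing references 4-7, so that "we will need a total sample size of 500 patients". F3 fixes the interval method: "Corresponding 95% exact binomial confidence intervals will be computed".

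References 4-7 are cited as a group in one other place, section B1. There they support the statement that "only 10% of these patients are ultimately diagnosed with an acute coronary syndrome (ACS", made about patients presenting to an ED with chest pain. The Background of the abstract (A1) puts the figure slightly lower: "less than 10% of these patients are ultimately diagnosed with ACS". Neither place says that STEMI patients were left out.

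The study population is narrower. ST elevation or STEMI is an exclusion in A1 Methods, in the D3 exclusion criteria, in D4 and in J1. The Participation text in D3 says "we expect less than 5% of patients with acute chest pain to be excluded due to ECG criteria". D3 also excludes patients with unstable vital signs. The outcome in E2 is a 30-day composite of cardiac death, acute myocardial infarction and coronary revascularization.

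**The concern.** The planning rate differs from its apparent source in two ways. The source figure is for ACS and the endpoint is MACE. The source population is described without a STEMI exclusion and the study population has one. If the 10% includes STEMI, excluding those patients removes cases from it, and the same 10% cannot simply be carried over. F2 makes no adjustment, and nowhere does the protocol give a MACE rate for ambulance-transported patients without ST elevation.

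Precision of the sensitivity estimate depends on the number of patients with MACE, not on the 500. A shortfall in events widens the interval directly. F1 presents the results as the basis for later changes to prehospital triage and destination plans, so a reader of F2 should be able to see what precision the enrolled patients can realistically deliver.

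**Working it through.** **Inputs.** From F2: 50 events, a 10% rate, 500 patients, and a target of 98% with a lower bound above 90%. From F3: exact binomial 95% intervals (Clopper-Pearson). From D3: fewer than 5% excluded on ECG, which is an upper limit and not an estimate. From B1 and A1: ACS in 10%, or less than 10%. Assumed here: a share s of chest pain patients has STEMI, all of them are inside the 10%, and all of them would be events.

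**Step 1: the plan's own figure.** 50 / 0.10 = 500. The arithmetic reproduces, so the question is only whether the 10% applies. If it does apply exactly, the chance of at least 50 events in 500 is 0.52.

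**Step 2: what removing STEMI would do.** The remaining rate is (0.10 − s) / (1 − s), and expected events are 500 times that rate.

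| Assumed s | Remaining rate | Expected events in 500 | Chance of at least 50 events |
|---|---|---|---|
| 0% | 10.0% | 50 | 0.52 |
| 1% | 0.09/0.99 = 9.1% | 45.5 (taken as 45) | 0.26 |
| 2% | 0.08/0.98 = 8.2% | 40.8 | 0.08 |
| 3% | 0.07/0.97 = 7.2% | 36.1 | 0.01 |
| 5% (limit) | 0.05/0.95 = 5.3% | 26.3 | essentially 0 |

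Read the other way, keeping 10% among eligible patients needs an all-comer rate of 0.10(1 − s) + s. That is 10.9% at s = 1% and 12.7% at s = 3%, both above the figures in B1 and A1.

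**Step 3: exact 95% lower bound for sensitivity.** With no misses among n events the bound is 0.025^(1/n). With one miss it is the value L that solves n·L^(n−1)·(1 − L) + L^n = 0.025.

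| Events n | One miss | No misses |
|---|---|---|
| 54 | 90.1% | 93.4% |
| 50 | 89.4% | 92.9% |
| 45 | 88.2% | 92.1% |
| 40 | 86.8% | 91.2% |
| 36 | 85.5% | 90.3% |
| 35 | 85.1% | 89.997% |
| 26 | 80.4% | 86.8% |

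Two thresholds follow. Below 36 events, the bound cannot exceed 90% even with no misses. With one miss, the bound first exceeds 90% at 54 events.

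**Step 4: the other reading of B1.** The B1 sentence can also be read as 10% of the patients admitted, whom it puts at almost two thirds of the total. Then the all-comer figure is about 0.10 × 2/3 = 6.7%, or 33 events in 500 before any STEMI exclusion. The bounds are 84.2% with one miss and 89.4% with none. The text does not settle which reading is meant.

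**The case against.** The strongest reply is that F2 openly labels the rate an assumption and that its direction of error is unknown. MACE in E2 is not a subset of index ACS. It leaves out unstable angina without infarction or revascularization. It adds any revascularization within 30 days, any infarction meeting the universal definition, and deaths from heart failure or arrhythmia. Ambulance patients may also be at higher risk than ED patients in general. This stands: the true rate could be 10% or more. A reader might infer that 500 patients will give fewer than 50 events, but the protocol does not support that. It does not say that the 10% includes STEMI, and the cited sources are not at hand.

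Three further inferences also go too far.

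- **About 26 events should be expected.** This takes the D3 upper limit as if it were met exactly and treats every ECG exclusion as a true event. It is a worst case.
- **The event rate is why one miss breaks the 90% target.** It is not. At the planned 50 events, 49 of 50 already gives 89.4%. That is a separate weakness of the 50-event figure, and fewer events make it worse.
- **Incomplete follow-up of up to 10% removes a further tenth of the events.** E1 takes index outcomes from the hospital record for all participants, and events found on record review count even when the patient cannot be reached. The loss of events cannot be quantified from the protocol.

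It is also fair to say that this is an observational pilot. F3 will report exact intervals on whatever events occur, and F1 sets no numerical lower bound for proceeding. That limits the consequence but does not make the F2 derivation sound.

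**Conclusion.** The point holds as a gap in justification. F2 attributes a 10% MACE rate to references that B1 uses for 10% ACS with no STEMI exclusion stated, and applies it to a population from which ST elevation is excluded. The protocol therefore does not show that 500 eligible patients supply 50 events, and it does not show that they will fall short.

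The size can only be illustrated. With STEMI at an assumed 1% to 3% of chest pain patients, all inside the 10% and all events, the expected count is 45 to 36. The exact lower bound is then 88.2% to 85.5% with one miss and 92.1% to 90.3% with none. With no misses the target is therefore still reachable over that range. It becomes unreachable only below 36 events, which needs either a STEMI share above about 3% or the admitted-patients reading of B1.

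**What to change.** Rewrite the sample-size paragraph in F2 and keep 500 patients.

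1. Stop attributing a 10% MACE rate to references 4-7. Label the rate as an assumption for the eligible population without ST elevation, or base it on the institution's own non-STEMI chest pain data. The protocol says the HEART Pathway has been standard there since November 2014, but it reports no MACE rate from that use.
2. Replace the statement that 500 patients provide the 50 events needed with the exact 95% lower bound over a range of event counts, each labelled as assumed. Include the planned case: at 50 events the bound is 89.4% with one miss and 92.9% with none. State that below 36 events the bound cannot exceed 90%.

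The cost is one rewritten paragraph, with no added patients, procedures or analyses. The downside is that the stated precision becomes less favourable than F2 now suggests.

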In addition to electronic surveillance, follow up phone calls will be used to determine outcomes at 30 days. EMS or project staff will contact each participant at 30-90 days following their pre-hospital encounter using a modified version of a previously described scripted follow-up dialogue[^23^](#_ENREF_23) to further clarify events since discharge, identify events occurring at other care facilities, and to determine health care utilization since discharge. Events of interest will include MACE (cardiac death, acute myocardial infarction, and coronary revascularization), hospitalizations, and objective cardiac testing (stress testing and coronary angiography), and recurrent ED visits. Participants still unable to be contacted will be considered censored at their last known contact unless record review reveals an event occurred, in which case the patient will be considered to have experienced an event. Participants unable to be contacted will be searched for in the Social Security Death Master File. In the event of discrepancy between a participant’s event reporting and the medical record, the medical record will be considered correct.

*Rationale for phone follow up:*  In order to determine the accuracy of paramedic HEART Score assessments for MACE we will need to have a low lost-to-follow-up rate. Without telephone follow-up calls patients who seek follow-up or recurrent care or have adverse events at non-WFBH facilities will not be detected. Furthermore, it is common practice for EMS agencies to use phone follow up to contact patients for quality assurance purposes. Using the above methods we expect to have a lost to follow-up rate less than 10%.

E2. Outcomes

*2a. Primary Outcome*

The primary outcome is MACE at 30 days. MACE is a composite outcome of cardiac death, acute myocardial infarction, and coronary revascularization. MACE occurring in patients with a low-risk HEART score assessment will be considered missed MACE. The primary outcome will be used to determine the sensitivity, negative predictive value, specificity, positive predictive value, likelihood ratios, and accuracy for paramedic detection of MACE at 30 days using the HEART score with i-STAT POC troponin testing.

The definition of cardiovascular death will be based on the Action to Control Cardiovascular Risk in Diabetes (ACCORD) trial.[^24^](#_ENREF_24) Death from stroke will not be considered a cardiac death.

Modified ACCORD definition of Cardiovascular Death:

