## F4. Missing Outcome Data

Based on prior studies we expect >90% to have complete follow-up data from the EMR or phone follow up calls. Participants without follow up data will be searched for the Social Security Death Master File. Those with missing outcome data will be treated as censored and will be considered to have not had a safety event. A planed sensitivity analysis will be used to test this assumption.

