For the pilot implementation we anticipate a sample size of approximately 500 subjects accrued over a 12 month period. Based on prior studies we expect about 90% to have complete follow-up data. We intend to exclude subjects who were less than 21 years old at the time of their ED visit, were having an acute ST-segment elevation MI (STEMI), or were inter-facility transfers. We anticipate this population will consist of an equal proportion of male and female patients of mean age 56 years based upon our preliminary data. Subjects will likely have increased cardiovascular risk factors compared to a normal population of controls. Subjects may have a history of cardiovascular disease. No special populations of subjects will be included. No collaborating sites will identify subjects. Specific inclusion and exclusion criteria are:

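### The sample size of 500 is exactly 50 / 10%, with no allowance for incomplete follow-up, so slightly fewer than the required 50 observed MACE are expected, and the 90% lower bound is not met even at 50

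*Protocol*

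**What the plan says.** Section F2 states the aim as "we hope to demonstrate that paramedics are able to achieve 98% sensitivity for the detection of MACE". It ties the size to a sensitivity of 98% "with a lower bound of the 95% confidence interval that exceeds 90" per cent, and says that for this "we will need at least 50 patients with MACE events". It then goes from events to patients: "Assuming a 10% MACE rate among our chest pain population", "to include 50 patients with adverse events we will need a total sample size of 500 patients". Section F3 says that the confidence intervals will be exact binomial.

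Sections D1 and J1 give 500 as the number accrued. On follow-up, E1 says "Using the above methods we expect to have a lost to follow-up rate less than 10" per cent, F4 expects more than 90% complete, and J1 says "Based on prior studies we expect about 90% to have complete follow-up data". For patients without an outcome, F4 says: "Those with missing outcome data will be treated as censored and will be considered to have not had a safety event". F4 also plans a sensitivity analysis of that assumption.

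**The concern.** F2 words 50 events as a minimum, but its arithmetic delivers 50 only as an average, and only if the 30-day outcome is known for every accrued patient. The protocol does not expect that. Under F4 a MACE that is never seen is scored as no event, so it drops out of the denominator of sensitivity. Any loss that hides an event therefore pulls the expected observed count below the stated requirement, because there is no margin.

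At stake is whether a reader can rely on the precision that F2 promises. The pilot is meant to support later changes to EMS triage and destination plans, so the precision statement should be one that the design can deliver.

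**Working it through.** **Inputs.** From F2: 50 events required, MACE rate 10%, target sensitivity 98%, 95% lower bound above 90%. From F3: exact binomial interval. From E1, F4 and J1: incomplete follow-up d up to about 0.10. Assumed, not in the documents: the share f of MACE that occurs after the index visit, taken as 20% to 50%; all such events unseen in lost patients; the same MACE risk in lost and followed patients.

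**1. The plan's own figure.** N = events / rate = 50 / 0.10 = 500. This reproduces F2 exactly and leaves no term for loss.

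**2. Expected observed events after loss.** Expected count = 500 × 0.10 × (1 − d × f).

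| d | f | Expected observed MACE | P(at least 50) |
| --- | --- | --- | --- |
| 0 | any | 50 | 52% |
| 0.10 | 0.20 | 50 × 0.98 = 49.0 | 46% |
| 0.10 | 0.30 | 50 × 0.97 = 48.5 | 43% |
| 0.10 | 0.50 | 50 × 0.95 = 47.5 | 37% |
| 0.10 | 1.00 (bound) | 50 × 0.90 = 45.0 | 24% |

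The last column is the binomial tail P(X ≥ 50) with n = 500 and p = 0.10 × (1 − d × f). At d = 0.05 and f = 0.50 the expected count is 50 × 0.975 = 48.75. The last row would need index-visit MACE in lost patients to go unseen as well.

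**3. The count is random even without loss.** For X ~ Binomial(500, 0.10), P(X ≥ 50) = 0.522 and the central 95% range is 37 to 64. The required minimum is therefore missed nearly half the time with perfect follow-up.

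**4. The precision claim.** With one miss in n events, the exact two-sided 95% lower bound is the 2.5% quantile of Beta(n − 1, 2).

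| Events | Observed sensitivity | Exact lower bound |
| --- | --- | --- |
| 40 | 39/40 = 97.5% | 86.8% |
| 45 | 44/45 = 97.8% | 88.2% |
| 48 | 47/48 = 97.9% | 88.9% |
| 49 | 48/49 = 97.96% | 89.1% |
| 50 | 49/50 = 98.0% | 89.4% |
| 54 | 53/54 = 98.1% | 90.1% |

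At 50 events and 98% observed sensitivity the bound is 89.4%, not above 90%. The smallest count that passes with one miss is 54. Other methods at 49/50 give 89.5% (Wilson), 90.9% (one-sided exact), 91.0% (Jeffreys) and 94.1% (Wald). The last three would pass, but F3 names the exact interval and F2 speaks of a 95% interval. With no miss at all, 50/50 has an exact bound of 92.9%.

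Losing one or two events moves the one-miss bound only from 89.4% to 89.1% or 88.9%. The 90% shortfall is therefore not caused by loss to follow-up.

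**The case against.** The strongest reply is that the protocol's ascertainment leaves little room for loss. Every patient goes to WFBMC, whose records track index outcomes and 30-day events within the WFBH system. E1 says that an uncontacted patient counts as having an event if record review finds one, and the Social Security Death Master File is searched as well. Only a non-fatal event outside WFBH after the index visit, or a death not found in that file, in a patient not reached by phone, can be missed. This stands. It makes 45 events an unlikely bound and the true shortfall small. It does not make the shortfall zero, since E1 itself justifies the phone calls by events at other facilities.

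It also stands that 10% is a ceiling in E1 and F4 and a central figure only in J1, that sizing on an expected event count is common, that 50 / 0.10 is computed correctly, and that this is an observational pilot. The sensitivity analysis in F4 tests the no-event assumption afterwards; it does not support the size.

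Two stronger readings are tempting. A reader might infer that, because one miss in fewer than 50 events falls below 98%, loss sharply cuts the chance of success: with a true sensitivity of 98%, the chance of observing at least 98% is 74% at exactly 50 events and 40% at exactly 45. That contrast comes from the sawtooth of a discrete proportion; 49 events give 37%. Averaged over the random event count, the chance is 56% with no loss, 52% to 55% in the post-index scenarios and 49% at the bound. F2 also sets no pass/fail rule on the point estimate. A reader might also infer that 500 / 0.90 = 556 patients are needed. That figure assumes that every event in lost patients is unseen, and its 50 expected events would still not give a one-miss bound above 90%.

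**Conclusion.** The concern holds at modest size. F2 makes no allowance for the protocol's own expected incomplete follow-up, so the expected number of observed MACE lies slightly below the stated requirement: about 47.5 to 49 at 10% loss, with 45 as an unlikely bound. These figures rest on F2's 10% MACE rate, on 10% loss (the top of the stated range), and on the assumed 20% to 50% share of post-index events.

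Two further facts need no assumption about loss. The figure of 50 is an expected count, reached or exceeded with probability 52%. And the promised bound above 90% fails at 49/50 under the interval that F3 names. It would be wrong to attribute that second failure to loss to follow-up. The documents do not support a claim that the pilot is materially undersized, or that loss alone defeats its aim.

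**What to change.** Reword F2, dropping both the fixed minimum of 50 events and the claim of a bound above 90%. Suggested text:

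*500 accrued patients at a 10% MACE rate give an expected 50 events before loss and slightly fewer (about 47 to 49; 45 at worst) after up to 10% incomplete follow-up. The count is random (about 37 to 64 before loss). With one missed event, the exact 95% lower bound for sensitivity is 86.8% at 40 events, 88.2% at 45 and 89.4% at 50.*

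State beside it the assumed share of post-index events behind the 47 to 49. The cost is wording only: no extra patients and no change in procedures. The stated precision becomes slightly less favourable than the present text.
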